### Sample size calculation

The sample size calculation was based on internal audit data showing a PTM rate of <2% in those treated with prophylactic radiotherapy who underwent ‘large’ bore procedures, in comparison to a rate of between 8% and 40% in the published literature of patients not undergoing prophylactic radiotherapy.

Assuming the rates of PTM to be 2% in the intervention group and 15% in the ‘control’ group, 180 patients are required to demonstrate a difference between treatment arms with 90% power at the 5% significance level. With an estimated lost to follow-up rate of 3%, this number is increased to 185 patients randomised 1:1. Various power modelling scenarios were considered (see table 1), demonstrating adequate power with varied control and intervention event rates if 203 patients are recruited.

**Table 1 BMJOPEN2014006673TB1:** Sample size calculations for different predicted PTM rates

	Control group As needed radiotherapy					
Intervention group Prophylactic radiotherapy	90% power (α 0.05, 3% loss to FU)			80% power (α 0.05, 3% loss to FU)		
Incidence of PTM at 12 months (%)	12	15	18	12	15	18
1	203	150	118	153	112	88
2	269	185	140	201	140	105
3	357	234	169	266	174	125
4	482	294	203	360	220	152
5	670	375	248	500	281	184

All rates include a projected 3% loss to follow-up. The figures in the shaded cells are those which are achievable within the proposed sample size.

FU, follow up; PTM, procedure tract metastasis.

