### Primary outcome

The primary outcome will be the difference in the incidence of development of PTM within 7 cm of the site of pleural intervention within 12 months from randomisation between the study arms.

A PTM will be defined as a clinically palpable nodule of at least 1 cm diameter felt within 7 cm of the margins of the procedure site as confirmed by two assessors. One of the assessors must be a doctor who feels that clinically the nodule is a tract metastasis. The assessors will be doctors, nurses or radiographers who have read the chest wall examination standard operating procedure (SOP) (see online supplementary appendix 6) and feel confident to undertake the examination. In the event of disagreement between the assessors, they will examine the patient together to reach a consensus.

The presence or absence of PTM within 12 months of randomisation will be compared using Fisher's exact test. This was chosen in preference to ‘time-to-event’ analysis for the primary outcome analysis, as prophylactic radiotherapy is not likely to change the speed with which the events occur, but rather prevent them from occurring, thereby violating the necessary assumptions of survival models. Time-to-event data will be modelled using regression analysis, but this will form part of the secondary analysis.

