### Statistical analysis plan

The full statistical analysis plan can be viewed in online supplementary appendix 7. The analysis will be based on intention-to-treat principles.

For continuous outcomes, analyses will adjust for the minimisation factors and the outcome measured at baseline (provided there is no substantial missing baseline data). For binary outcomes, if the number of events allows, the analysis will adjust for the minimisation factors. If major baseline imbalances between the treatment arms are identified, these may also be adjusted for in the regression models.

For missing baseline data, if the numbers are small, median imputation will be used. If the numbers with missing data are large, alternative analysis methods may be used, which do not account for baseline values.

CONSORT data will be presented including the number of patients screened for the study and the numbers randomised. Reasons for exclusions after randomisation will be given.

Analysis for all outcomes will be presented as:
The number of participants included in the analysis, by treatment group;A summary statistic for the outcome, by treatment group (eg, mean (SD) or median (2.5th–97.5th centile) for continuous outcomes; number (%) for binary outcomes);A treatment effect, with a 95% CI and p value (2 sided; the significance level set at 5%).

The primary outcome, incidence of PTM within 12 months, will be analysed on an intention-to-treat basis. The proportion of patients developing a PTM (as defined above) within 12 months from randomisation or until death or loss to follow-up (whichever is sooner) will be calculated for both trial arms and compared using Fisher’s exact test. Alternatively, if the number of events allows, logistic regression will be performed, adjusting for the minimisation variables and any substantial baseline imbalances.

A secondary, per protocol analysis will be performed for the primary outcome, excluding patients with major protocol violations.

If numbers allow, the following subgroup analyses will be performed for the primary outcomes:
By the type of pleural intervention randomised (large bore chest drain, local anaesthetic thoracoscopy, IPC or thoracic surgery);By tumour subtype (epithelioid only or other);Patients who were alive and in trial follow-up for at least 6 months (yes/no);Patients who received chemotherapy for mesothelioma within 12 months from trial entry (yes/no).

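### The stated sample sizes follow a large-sample formula but the primary test is Fisher's exact test, so some stated powers are slightly too high at equal allocation; the design case at 203 patients is safe

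*Protocol article*

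**What the plan says.** All references are to the protocol article.

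- **Primary outcome** names the test: "The presence or absence of PTM within 12 months of randomisation will be compared using Fisher's exact test".
- **Statistical analysis plan** repeats Fisher's test and sets the level: "A treatment effect, with a 95% CI and p value (2 sided; the significance level set at 5"%). It also allows another route: "Alternatively, if the number of events allows, logistic regression will be performed, adjusting for the minimisation variables and any substantial baseline imbalances".
- **Sample size calculation** starts from 2% with prophylactic radiotherapy and 15% in the control group and says "180 patients are required to demonstrate a difference between treatment arms with 90% power at the 5% significance level". It then adds the loss allowance: "With an estimated lost to follow-up rate of 3%, this number is increased to 185 patients randomised 1:1".
- The step from 185 to 203 rests on Table 1, which covers control rates of 12%, 15% and 18% and radiotherapy rates of 1% to 5%, at 90% and 80% power. The text describes it as "demonstrating adequate power with varied control and intervention event rates if 203 patients are recruited". The table note adds: "All rates include a projected 3% loss to follow-up".

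Neither the text nor the table names the test or formula behind the sample sizes.

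**The concern.** At event rates this low, Fisher's exact test is conservative. With equal arms of 98 and a common rate of 8.5% (midway between 2% and 15%), its actual two-sided error rate is about 2.7%, not 5%. A sample size from an uncorrected large-sample formula therefore buys less power than its label says.

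Two statements are affected. One is the requirement of 180 evaluable patients for the base case. The other is the claim that 203 patients cover a range of scenarios. The text itself requires only 185, so 203 depends on the cells at the edge of Table 1: 1% v 12% and 4% v 18% at 90% power (both exactly 203) and 2% v 12% at 80% (201). If the trial shows no difference, readers will look to these statements to judge what it could have detected.

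**Working it through.** **Inputs.** From Sample size calculation: base-case rates 2% and 15%; 90% power; 180 evaluable and 185 randomised; 3% loss; 203 planned; the Table 1 cells. From Statistical analysis plan: two-sided 5%. From Randomisation: 1:1. The shading in Table 1 is lost, so the achievable cells are taken to be those with N of 203 or less.

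**Step 1: reproduce the plan's figures.** The unpooled normal approximation, per arm, is

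n = (z₀.₉₇₅ + z_power)² × [p₁(1−p₁) + p₂(1−p₂)] / (p₁ − p₂)²

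For 2% v 15% at 90% power: (1.960 + 1.282)² × (0.0196 + 0.1275) / 0.13² = 10.507 × 0.1471 / 0.0169 = 91.5. That is 92 per arm, 184 evaluable, and 184/0.97 = 190 randomised, against 180 and 185 in the text (within 3%).

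The same formula matches 29 of the 30 Table 1 cells within 3% when loss is applied as N/0.97, and all 30 when it is applied as N × 1.03. Alternatives fit worse:

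| Formula | Base case, evaluable | Cells matched (N/0.97) |
|---|---|---|
| Unpooled normal | 184 | 29 of 30 |
| Likelihood ratio | 174 | 21 of 30 |
| Pooled normal | 190 | 3 of 30 |
| Pooled, continuity-corrected | 220 | 0 of 30 |

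**Step 2: exact power under the named test.** Power is the sum of binomial probabilities over all 2×2 outcomes for which the two-sided Fisher p-value is at most 0.05. With equal arms the two usual two-sided definitions (minimum-likelihood, and twice the smaller one-sided value) give the same power.

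Base case, 2% v 15%:
- 90+90 (the stated 180): 87.9%.
- 95+95: 89.8%; 96+96: 90.2%. So 90% needs 192 evaluable, and 192/0.97 = 198 randomised.
- 203 × 0.97 = 197 evaluable; the nearest equal split, 98+98, gives 90.9%.

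Other scenarios at 98+98:

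| Radiotherapy v control | Printed N | Stated power | Fisher power, 98+98 | Needed: evaluable (randomised) |
|---|---|---|---|---|
| 1% v 12% | 203 | 90% | 88.4% | 204 (211) |
| 4% v 18% | 203 | 90% | 86.5% | 216 (223) |
| 2% v 12% | 201 | 80% | 75.0% | 216 (223) |
| 5% v 18% | 184 | 80% | 78.1% | 204 (211) |

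**Step 3: how stable this is.** The same calculation for all 197 evaluable patients, radiotherapy arm first:

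| Scenario | 98+99, min.-likelihood | 99+98, min.-likelihood | 98+99, doubled | 99+98, doubled |
|---|---|---|---|---|
| 2% v 15% | 91.4% | 94.1% | 90.2% | 91.1% |
| 1% v 12% | 89.0% | 92.9% | 88.3% | 88.3% |
| 4% v 18% | 87.2% | 90.3% | 86.2% | 87.3% |
| 2% v 12% | 75.9% | 82.1% | 73.7% | 75.0% |
| 5% v 18% | 79.1% | 83.2% | 77.6% | 78.9% |

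The jump at 99+98 comes from the minimum-likelihood definition. When the radiotherapy arm is slightly larger, the mirror-image table is a little more probable than the observed one and drops out of the p-value. A simple average over the eight splits from 95+102 to 102+95, with that definition, leaves 4% v 18% at about 89% and 2% v 12% at about 79%. The averages for 1% v 12% (91.0%) and 5% v 18% (81.2%) are above nominal.

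**The case against.** The strongest reply is that the shortfall can turn on one patient. Minimisation with a random component does not fix the final split. At 99 radiotherapy and 98 control, with the minimum-likelihood p-value, all four scenarios meet their stated power. Even the base case at 180 rises from 87.9% at 90+90 to 91.7% at 91+89. This stands, and it rules out saying flatly that the boundary cells fail or should be struck from the table. It does not rescue the printed figures. At exactly equal arms all four are short, and with the doubled p-value they stay short at 98+99 and 99+98 too. Power that depends on one split and one p-value definition should not be stated without that condition.

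Second, the article permits adjusted logistic regression, for which a large-sample formula is less out of place. That route is conditional on the number of events and is not given as the basis for the sample size. Fisher's test remains the named primary comparison.

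Third, the text claims adequate power, not 90% in every cell. That is fair to the sentence, but the Table 1 columns are headed 90% and 80%.

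A reader might also infer that Table 1 is wrong to start at a 12% control rate, since the text cites published rates from 8% and both later trials in the Introduction had 10% in the control arm. The article discloses its range and its chosen 15%, and one of those trials mixed small and large bore procedures. Which rates to tabulate is a design choice, separate from the mismatch between formula and test.

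**Conclusion.** The point holds in a limited form. For a two-sided Fisher's exact test at 1:1, the requirement of 180 evaluable (185 randomised) is wrong as written: it gives 87.9%, and 90% needs 192 (198). At 203 randomised the shortfall at equal arms is 5.0 points for 2% v 12% and 3.5 points for 4% v 18%. For 1% v 12% and 5% v 18% it is 1.6 and 1.9 points, which is marginal.

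A reader might conclude that the trial is underpowered or needed more patients. The figures do not support that: the base case has about 91% power at 203, and at least 90% at each near-equal split examined under either p-value definition.

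The conclusion rests on three assumptions: the sizing formula is inferred by reproduction, 3% loss leaves 98 per arm, and the achievable cells are those with N of 203 or less. Applying the loss as 180 × 1.03 = 185 instead of 180/0.97 = 186 makes no material difference.

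**What to change.** 1. In Sample size calculation, name the method and restate the base case for Fisher's test: 192 evaluable, 198 randomised for 90% power, with about 91% at the planned 203.
2. Recompute Table 1 with exact Fisher power at equal arms. State which two-sided p-value definition is used and give the range over near-equal splits.
3. Describe the boundary scenarios, chiefly 2% v 12% and 4% v 18%, as slightly below their nominal power at 203 instead of as achieved.

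This costs a text and table correction and makes a few stated figures less favourable. It needs no extra patients, no additional control-rate columns and no change of primary test. Recruitment has closed and the trial is in follow-up, so nothing in its conduct changes.

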### Statistical analysis plan

The full statistical analysis plan can be viewed in online supplementary appendix 7. The analysis will be based on intention-to-treat principles.

For continuous outcomes, analyses will adjust for the minimisation factors and the outcome measured at baseline (provided there is no substantial missing baseline data). For binary outcomes, if the number of events allows, the analysis will adjust for the minimisation factors. If major baseline imbalances between the treatment arms are identified, these may also be adjusted for in the regression models.

For missing baseline data, if the numbers are small, median imputation will be used. If the numbers with missing data are large, alternative analysis methods may be used, which do not account for baseline values.

CONSORT data will be presented including the number of patients screened for the study and the numbers randomised. Reasons for exclusions after randomisation will be given.

Analysis for all outcomes will be presented as:
The number of participants included in the analysis, by treatment group;A summary statistic for the outcome, by treatment group (eg, mean (SD) or median (2.5th–97.5th centile) for continuous outcomes; number (%) for binary outcomes);A treatment effect, with a 95% CI and p value (2 sided; the significance level set at 5%).

The primary outcome, incidence of PTM within 12 months, will be analysed on an intention-to-treat basis. The proportion of patients developing a PTM (as defined above) within 12 months from randomisation or until death or loss to follow-up (whichever is sooner) will be calculated for both trial arms and compared using Fisher’s exact test. Alternatively, if the number of events allows, logistic regression will be performed, adjusting for the minimisation variables and any substantial baseline imbalances.

A secondary, per protocol analysis will be performed for the primary outcome, excluding patients with major protocol violations.

If numbers allow, the following subgroup analyses will be performed for the primary outcomes:
By the type of pleural intervention randomised (large bore chest drain, local anaesthetic thoracoscopy, IPC or thoracic surgery);By tumour subtype (epithelioid only or other);Patients who were alive and in trial follow-up for at least 6 months (yes/no);Patients who received chemotherapy for mesothelioma within 12 months from trial entry (yes/no).

Full details of the analysis of the secondary outcomes can be found in statistical analysis plan (see online supplementary appendix 7).

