### Randomisation

Following informed consent, patients will be randomly assigned (1:1) to receive either immediate prophylactic radiotherapy (within 42 days of the pleural intervention) or deferred radiotherapy (given if the patient develops a PTM).

Treatment allocation will be performed over the telephone by UKCRC Oxford Respiratory Trials Unit. The randomisation sequence will be generated using a validated, online randomisation service (Sealed Envelope, London, UK; http://www.sealedenvelope.com). Minimisation with a random component will be used to reduce the baseline between-group differences.

The minimisation factors are:
Histological tissue type of mesothelioma (epithelioid only or other);IPC or other pleural procedure;Surgical procedure (ie, open pleural biopsy, thoracotomy or VATS) or non-surgical procedure.

Patients and clinicians will not be blinded to treatment allocation; however, the data analysis will be conducted in a blinded fashion.

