### Data collection and management

#### Randomisation visit

Clinical data will be collected at the randomisation visit. This will include a history and chest wall examination and patients will be asked to complete two quality of life questionnaires (EQ5D and QLQ-C30) and visual analogue scale (VAS) scores to quantify their current degree of chest pain.

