### Secondary outcomes

Specific details regarding all the secondary outcomes can be found in the statistical analysis plan in online supplementary appendix 7. The secondary outcomes will include:
The change in chest pain VAS scores from randomisation to 12 months postrandomisation between the study arms;The change in quality of life (as measured by EQ5D and QLQ-C30) from randomisation to 12 months postrandomisation between the study arms;The difference in analgaesia requirements between the study arms;The difference in the size, symptom severity and time to development of PTM between the study arms;The rate and severity of radiotherapy toxicity;The number of serious adverse events (SAEs) related to radiotherapy or a PTM;The health economic implications of immediate and deferred radiotherapy;The identification of emergent themes from the semistructured interviews.

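### The plan allows the baseline covariate to be dropped for every patient when many baseline values are missing, a loss of precision in the continuous secondary outcomes that its own imputation rule would largely avoid

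*Protocol article*

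**What the plan says.** The Statistical analysis plan section of the protocol article has three linked statements on baseline values.

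- Default for continuous outcomes: "analyses will adjust for the minimisation factors and the outcome measured at baseline (provided there is no substantial missing baseline data".
- Few values missing: "For missing baseline data, if the numbers are small, median imputation will be used".
- Many values missing: "If the numbers with missing data are large, alternative analysis methods may be used, which do not account for baseline values".

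The outcomes concerned are listed under Secondary outcomes, and both are defined as changes: "The change in chest pain VAS scores from randomisation to 12 months postrandomisation between the study arms" and "The change in quality of life (as measured by EQ5D and QLQ-C30) from randomisation to 12 months postrandomisation between the study arms". On timing, the Randomisation visit section says only that "Clinical data will be collected at the randomisation visit". It lists the two quality of life questionnaires and the chest pain VAS among the measures taken there. The Randomisation section says that patients and clinicians are not blinded to allocation but that the data analysis is.

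**The concern.** The only approach named for extensive missingness sets aside every baseline value, including those that were recorded. Imputation is kept for the case where few values are missing, as if it ceased to be valid when many are. In a randomised trial it does not. If baseline is recorded before allocation is known, neither the baseline value nor whether it is missing can depend on arm, so a covariate filled with a single value is still a legitimate pre-randomisation covariate. More missing data makes the covariate less useful but does not make it biasing.

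At stake is the width of the confidence intervals for chest pain and quality of life, which answer the article's secondary questions on symptoms, quality of life and the impact of toxicity. The fallback also fits poorly with outcomes defined as change from randomisation, because a method that ignores baseline does not use that change.

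**Working it through.** **Figures in the plan.** The article gives no precision or power for the continuous outcomes, so there is no stated figure to reproduce on this point. Its only calculation is for the primary outcome (2% against 15%, 90% power, two-sided 5%). The unpooled normal approximation gives (0.15×0.85 + 0.02×0.98)×(1.960 + 1.282)²/0.13² = 91.5 per arm, or 184 in total after rounding up each arm, against the stated 180. That agrees within 3%, and nothing below affects it.

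**Inputs.**
- Allocation 1:1 (Randomisation section).
- 203 patients with 3% loss (Sample size calculation): 203×0.97 ≈ 197.
- r, the correlation between baseline and follow-up score: not given, assumed 0.3, 0.5 and 0.6. It is best read as what remains after the minimisation factors, which can stay in the model either way.
- m, the share of patients with no baseline: not given, assumed 20%, 30% and 50%.

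**Formula.** Set the residual variance without baseline to 1. With single-value imputation plus an indicator, the share 1−m with a recorded baseline has residual variance 1−r², and the share m without one has residual variance 1. The pooled value is

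V = (1−m)(1−r²) + m = 1 − r²(1−m).

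Dropping baseline inflates the variance of the treatment effect by 1/V − 1 and widens the interval by 1/√V − 1. For r = 0.5 and m = 20%: V = 0.8×0.75 + 0.2 = 0.80, so variance rises by 1/0.80 − 1 = 25% and the interval widens by 11.8%.

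| r | m | V | Variance inflation | Interval wider by |
|---|---|---|---|---|
| 0.3 | 20% | 0.928 | 7.8% | 3.8% |
| 0.3 | 30% | 0.937 | 6.7% | 3.3% |
| 0.3 | 50% | 0.955 | 4.7% | 2.3% |
| 0.5 | 20% | 0.800 | 25.0% | 11.8% |
| 0.5 | 30% | 0.825 | 21.2% | 10.1% |
| 0.5 | 50% | 0.875 | 14.3% | 6.9% |
| 0.6 | 20% | 0.712 | 40.4% | 18.5% |
| 0.6 | 30% | 0.748 | 33.7% | 15.6% |
| 0.6 | 50% | 0.820 | 22.0% | 10.4% |

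At r = 0.5 and m = 30%, dropping baseline costs about 197×(1 − 0.825) ≈ 34 patients' worth of information. The ratio V does not depend on the number of patients, so it also holds for a smaller number with follow-up scores.

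**Check by simulation.** Trials of 197 patients, 3,000 runs per setting, were simulated with r = 0.5 and 0.7 and m = 20%, 30% and 50%. Missingness was either random or dependent on the baseline value itself.

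- Bias was at most 0.005 SD and interval coverage 94% to 96%, both for median imputation alone and for imputation plus indicator.
- Variance relative to dropping baseline was 0.60 to 0.88 with the indicator and 0.62 to 0.90 with median imputation alone.
- At r = 0.5 and m = 30% the values were 0.82 to 0.83 with the indicator and 0.81 to 0.86 with median imputation alone, against 0.825 from the formula.

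So the plan's own small-numbers rule keeps most of the available gain at every level of missingness examined. The indicator helps mainly when missingness depends on the baseline value.

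**The case against.** Several objections are fair and limit the point.

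- **The wording is permissive.** The article says such methods may be used. A reader might infer that the plan requires baseline to be dropped; it does not. The proviso on the default model makes adjustment conditional, but no level of missingness triggers a mandatory drop.
- **No cut-off is shown.** A reader might infer that small, large and substantial are undefined and that the model will be picked after seeing the results. The document does not support that. It refers to a full analysis plan in an appendix that is not shown, where a threshold may stand, and it says the analysis will be blinded. The absence of a threshold is not part of this point.
- **Validity is intact.** An analysis without baseline is still unbiased under randomisation, and the article allows adjustment for important baseline imbalances.
- **The scenario may not arise.** Baseline measures are taken at one attended visit and missing data are queried monthly. Nothing suggests that 20% or more will be missing.
- **The loss is smallest where the fallback is most likely to be used.** At 50% missing it is 4.7% to 22% of variance over the assumed correlations, and at r = 0.3 it is minor throughout.
- **The remedy has a condition.** It needs missingness to be independent of allocation. Treatment is open-label, and the article does not say whether the questionnaires are completed before allocation is disclosed.
- **Other methods would serve.** A repeated-measures model with baseline in the outcome vector also keeps the recorded values.

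What survives is that the article names, for extensive missingness, only an approach that wastes recorded data. That is stated text and not a detail left to the unseen plan.

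**Conclusion.** The point holds as a modest matter of efficiency. The plan permits recorded baseline values to be ignored when many others are missing, and there is no statistical need for this if baseline precedes knowledge of allocation. Under assumed correlations of 0.3 to 0.6 and 20% to 50% missing, the price is a variance inflation of roughly 5% to 40%, or intervals about 2% to 18.5% wider. Both ranges rest on assumptions, since the document supplies neither quantity.

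The effect is confined to chest pain VAS, EQ5D and QLQ-C30. It would be wrong to infer any bias in the treatment effect, or any consequence for the primary comparison of procedure tract metastasis, which has no baseline value because a qualifying nodule at entry is an exclusion. The sample size is likewise untouched.

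**What to change.** Delete both the proviso on baseline adjustment and the option that ignores baseline, and put one rule in their place:

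- Every continuous outcome is adjusted for its baseline value and the minimisation factors.
- A missing baseline is filled with the overall median, not the median by arm, and a missing-value indicator is added, whatever the number missing.
- The follow-up score is modelled, not the change, so that patients without a baseline stay in the analysis.

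Also confirm, and state, that the baseline questionnaires are completed before allocation is disclosed.

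The cost is a short edit, one extra parameter per outcome and reliance on that ordering. No new data are needed. The article reports that recruitment has closed and follow-up is continuing, so the rule can be fixed before the final analysis.

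### The article names Fisher's test as the primary analysis in one section and in another lets a logistic regression, with covariates partly chosen from the data, take its place

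*Protocol article*

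**What the plan says.** All statements are in the protocol article.

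- **Primary outcome:** "The presence or absence of PTM within 12 months of randomisation will be compared using Fisher's exact test". The section explains why this was preferred to a time-to-event analysis and names no other primary test.
- **Statistical analysis plan, primary-outcome paragraph:** the proportions with PTM "will be calculated for both trial arms and compared using Fisher’s exact test". The next sentence reads: "Alternatively, if the number of events allows, logistic regression will be performed, adjusting for the minimisation variables and any substantial baseline imbalances".
- **Statistical analysis plan, general rules:** "For binary outcomes, if the number of events allows, the analysis will adjust for the minimisation factors", and "If major baseline imbalances between the treatment arms are identified, these may also be adjusted for in the regression models".
- **Randomisation:** "Minimisation with a random component will be used to reduce the baseline between-group differences". The three binary factors are histology (epithelioid only or other), IPC or other procedure, and surgical or non-surgical procedure. Patients and clinicians are not blinded, but "the data analysis will be conducted in a blinded fashion".

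The article refers to a full analysis plan in an online appendix, which is not at hand.

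**The concern.** The two sections do not describe the same primary analysis. One fixes an unadjusted exact test. The other offers that test or an adjusted model in its place; the sentence is worded as a replacement, not as a supporting analysis. The general rule for binary outcomes points the other way again, because it makes adjustment the norm once events suffice. So the default itself is unclear.

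The replacement depends on two things known only once data are in: the number of events, and which baseline variables turned out imbalanced between the arms. The second also decides what is in the model. The result changes in kind too, since an adjusted logistic model gives a conditional odds ratio, whereas the Primary outcome section defines the outcome as a difference in incidence.

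At stake is whether the headline verdict could turn on a choice that the published text leaves open.

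**Working it through.** **Inputs from the article (Sample size calculation).** PTM rates 2% v 15%, two-sided 5%, 90% power, 180 patients, 185 after 3% loss, target 203. Less 3%: 203 × 0.97 = 196.9, taken below as 98 per arm (196).

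**Step 1: the plan's own figure.** Normal approximation with unpooled variance:
n per arm = (1.960 + 1.282)² × (0.02×0.98 + 0.15×0.85) / 0.13² = 10.507 × 0.1471 / 0.0169 = 91.5.
This gives 92 per arm, 184 in all, against 180 stated; 184 / 0.97 = 190 against 185. Both agree within 3%, so the design figures are taken as they stand.

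**Step 2: is the event trigger a real decision?** Expected events are 98 × (0.02 + 0.15) = 16.7. Treatment plus three minimisation factors is four coefficients: 16.7 / 4 = 4.2 events per coefficient, before any imbalance covariate. Two competent analysts could answer differently.

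**Step 3: how often would the two tests disagree?** Full enumeration at 98 per arm, Fisher against an unadjusted likelihood-ratio (LR) logistic test. No covariate assumptions are needed. The LR form is an assumption, as the article does not name one.

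| True rates | Fisher significant | LR significant | Verdicts differ |
|---|---|---|---|
| 2% v 15% | 90.9% | 95.1% | 4.3% |
| 2% v 12% | 75.0% | 85.4% | 10.4% |
| 5% v 15% | 57.4% | 67.5% | 10.0% |
| 8.5% v 8.5% (null) | 2.7% | 5.4% | 2.6% |

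In these four scenarios every disagreement has LR significant and Fisher not.

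Two plausible outcomes at 98 per arm:
- 2 v 9 events: Fisher p = 0.058, Wald p = 0.047, LR p = 0.024.
- 5 v 14 events: Fisher p = 0.051, Wald p = 0.037, LR p = 0.027.

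**Step 4: type I error when the choice is open.** Simulation with 3,000 trials per scenario, 196 analysed and common rates of 8.5% to 15%. Assumed: three binary factors with prognostic odds ratios of 1 to 3 each, minimisation with probability 0.8, and a 10-point between-arm difference counted as an imbalance.
- Fisher alone: 2.7–4.1%.
- Adjusted logistic (LR) alone: 4.5–6.6%.
- Better of the two: 4.5–6.6%.
- Better of the two plus an imbalance-adjusted version: 4.8–7.1%.

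The Monte Carlo standard error near 5% is √(0.05×0.95/3000) = 0.4 percentage points.

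**Step 5: power if Fisher's test alone is named.** Exact power at 2% v 15% is 87.9% at 90 per arm and 90.9% at 98 per arm.

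**The case against.** **Details left to the analysis plan.** An event threshold and a definition of a substantial imbalance may well be in the appendix. That stands: their absence from the article is not the finding. What remains is that the article names one primary analysis in one section and two in another, and states covariate choice by observed imbalance as a rule.

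**Blinded analysis.** The event trigger can be judged on the pooled count without knowing the arms, so depending on the data does not mean depending on the effect. This largely stands for the event count. It is weaker for the covariates, because judging imbalance needs data split by arm, at least under coded labels.

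**Four stronger readings that a reader might infer, which the article does not support:**
- *The logistic option breaks down or loses power.* Zero events in the irradiated arm has probability 0.98⁹⁸ = 14% at the planned rate, and the maximum-likelihood odds ratio is then not finite. A Wald test used regardless has simulated power of only about 79% at 2% v 15% and 64% at 2% v 12%. But the model applies only if events allow, and zero events in an arm is the plain case where they do not, so Fisher's test stands. Using Fisher there and Wald otherwise gave 93% against 91% for Fisher alone at 2% v 15%, and 78% against 75% at 2% v 12% (simulated, assumed covariate prevalences).
- *Choosing between the tests seriously inflates type I error.* Step 4 shows that the better of the two adds almost nothing to the logistic test alone. The further rise comes from imbalance-chosen covariates and is small.
- *Fisher's test is invalid because it leaves out the minimisation factors.* Leaving them out tends to make the test conservative. It costs efficiency, not validity.
- *A particular method is required.* Cochran-Mantel-Haenszel (CMH), a prespecified adjusted model and Fisher's test are all defensible. The fault is in not settling on one.

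**Conclusion.** The concern holds as an inconsistency that leaves the primary analysis open to a data-dependent choice. The two sections must be reconciled.

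The practical size is the share of trials in which the choice decides significance: about 4% at the planned rates and about 10% at smaller effects. These figures are exact for 98 per arm but rest on the likelihood-ratio form of the logistic test and on no adjustment. The type I error figures, at worst about 7%, rest on the assumed prognostic effects, minimisation probability and imbalance cut-off. They show a modest excess over 5%.

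The open covariate clause is the weaker part of the plan; the event-count trigger is less serious given the blinding statement. This is a should-fix: it bears on the confirmatory conclusion, but neither candidate test is unsound in itself.

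**What to change.** Before unblinding, with the same wording in the Primary outcome and Statistical analysis plan sections (and in the full analysis plan, if it differs):

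1. Name one primary analysis. Preferably it uses the minimisation factors, for example a CMH test stratified by them with a Mantel-Haenszel risk difference and 95% CI, which matches the outcome defined as a difference in incidence. Otherwise keep Fisher's test, which retains about 91% power at 98 per arm for 2% v 15%.
2. Label the other analysis as a sensitivity analysis.
3. Restrict covariates in any adjusted analysis of the primary outcome to the three minimisation factors.
4. Delete adjustment for observed baseline imbalances from the primary analysis, in both the primary-outcome sentence and the general rule as it applies to this outcome.

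The cost is a change of wording and the loss of post-hoc flexibility. No further patients or data are needed. The Trial status section says that recruitment has closed and follow-up continues, so on the article's own account there is still time.
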